## Prospective statistical analysis

The statistical analysis of the DetECT study mainly focuses on comparing ECT responders with non-responders (internal control group) within the sample. Clinical response indicated by overall and sub-domain changes in psychometry will serve as main dependent variables and analyses focus on within-subject changes over time. On the one hand, we aim to use variance and correlation analyses (e.g., repeated-measures ANOVA, Pearson’s r and correlation matrices), regression models (e.g., linear or logistic regression), and principal component analysis to first identify both significant main and interaction effects between biobehavioral parameters and treatment response. These analyses will be performed for all measures pre-, during, and post-treatment. Aside from using single parameters and the area under the curve as independent variables, we will employ index and score approaches (e.g., inflammatory indexing and Z scores) to allow combined analyses of functionally connected processes. Following these steps, we plan to employ linear mixed models (LMM) to examine if a single or parameter cluster is linked to remission, treatment response, failure, and side effects. As described above, we will also use single and combined as well as over time parameters, indices, or scores to perform LMM. Factors like the SES, comorbidities, smoking, concomitant pharmacological treatment (both general and psychiatry specific), and mode of ECT application (e.g., right-unilateral vs. left-anterior-right-temporal) will be used as covariates. Multiple comparisons correction will be applied. To further ensure that the identified associations are not only statistically significant, but also represent a relevant underlying biological mechanism, we will report both significance (p value) as well as effect size (e.g., Cohen’s d or comparable measures) in prospective DetECT publications, as recommended for instance by Goodman et al. 2019 [161].

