In addition to the serial blood draws, participants are asked to answer the following self-rating questionnaires concerning their depressive and somatic symptoms on a weekly basis: Patient Health Questionnaires 9 and 15 (PHQ-9/-15) [122–125], the Questionnaire on Mental Capacity (FLei) [126], and the Beck Depression Inventory (BDI-II) [127–129]. The reference-interval of the self-rating questionnaires was customized from two (PHQ-9, BDI-II) and four (PHQ-15) weeks as well as six month (FLei) to the week prior to match the DetECT study design. Moreover, three clinician-rating instruments are assessed via a clinical interview in week 1, 4, and 7 of the study period: the Montgomery-Åsberg Depression Rating Scale (MADRS) [130, 131], the Hamilton Rating Scale for Depression with 21 items (HAM-D21) [132–134], and the DSM-IV derived Global Assessment of Functioning (GAF) [135, 136]. In addition to study related procedures, metabolic parameters (i.e., body mass index (BMI) or blood pressure (BP)) as well as medical information (e.g., patient and family anamnesis, past and recent medication including concomitant psychopharmacological treatment pre and during ECT allergies, drug use, psychiatric and somatic diagnoses) and sociodemographic data are extracted from patient records. See Fig. 1 for further detail.

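### Pre-treatment markers are related to symptom change without naming the starting score as a covariate, so a marker of starting severity can look like a predictor of ECT response

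*Protocol article*

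**What the plan says.** The Prospective statistical analysis section "mainly focuses on comparing ECT responders with non-responders (internal control group) within the sample". It then fixes the outcome: "Clinical response indicated by overall and sub-domain changes in psychometry will serve as main dependent variables and analyses focus on within-subject changes over time". It does not say whether a change is a difference, a percentage or a threshold.

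The first analysis step is described in one sentence: "we aim to use variance and correlation analyses (e.g., repeated-measures ANOVA, Pearson’s r and correlation matrices", followed by "regression models (e.g., linear or logistic regression), and principal component analysis to first identify both significant main and interaction effects". The scope is wide: "These analyses will be performed for all measures pre-, during, and post-treatment". Pre-treatment measures are therefore among those related to change. Linear mixed models come next.

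The covariates named are socioeconomic status, comorbid illness, smoking, concomitant medication and the mode of ECT. They are introduced as examples, so the list is open. The pre-ECT score is not among them, although the Introduction counts episode severity among the few clinical predictors of ECT success now in use.

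The starting scores exist. According to Study design and population, "three clinician-rating instruments are assessed via a clinical interview in week 1, 4, and 7 of the study period", and the self-ratings are weekly.

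**The concern.** A change score has the starting score inside it. Patients who start high tend to show larger falls through regression to the mean alone. A pre-treatment marker that is correlated with starting severity inherits that association, even if it says nothing more about where the patient ends up.

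This matters because the secondary hypothesis is about predicting and monitoring ECT outcome, and the article hopes for a clinical prediction tool. Inflammatory, metabolic and endocrine markers could plausibly track severity. The planned multiplicity correction and effect-size reporting do not remove the problem: the association with change is genuine but reflects the starting point. For a marker unrelated to severity, the cost is different: the unadjusted change score can be noisier than the baseline-adjusted outcome.

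**Working it through.** **Inputs.** From the Power calculation section: N = 134, α = 0.05 (taken as two-sided), power 0.80, d = 0.5. The 134 reproduces as a two-sided Mann-Whitney comparison with 67 per group (power 0.801); a t-test gives 128. It does not depend on baseline adjustment, so it serves here only as the N.

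The article gives no correlations or SDs. Assumed: ρ = start-end correlation (0.3 to 0.7); k = follow-up SD / baseline SD (1 or 1.5); r = marker-baseline correlation (0.2 to 0.4). The marker is linked to the later score only through the measured starting score.

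**Step 1: expected correlation of marker with raw change (later minus start).**

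corr = r × (ρk − 1) / √(1 + k² − 2ρk)

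- k = 1, ρ = 0.5, r = 0.3: 0.3 × (−0.5)/1 = −0.15.
- k = 1.5, ρ = 0.7, r = 0.3: 0.3 × 0.05/√1.15 = 0.014, practically nil.

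**Step 2: how often this is declared significant.** By Fisher's z in the first case: atanh(0.15) × √131 = 0.1511 × 11.45 = 1.73, and Φ(1.73 − 1.96) = 0.41. Simulation agrees (20,000 runs per cell). Percent change and a split at 50% reduction also need means; 32 (SD 6) at the start and 15 at the end are assumed.

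Rejection rates in % for r = 0.2 / 0.3 / 0.4, nominal 5%:

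| k | ρ | Raw difference | Percent change | 50% responder split |
|---|---|---|---|---|
| 1 | 0.3 | 27 / 54 / 79 | 7 / 10 / 14 | 7 / 9 / 12 |
| 1 | 0.5 | 21 / 42 / 65 | 5 / 6 / 6 | 5 / 5 / 5 |
| 1 | 0.7 | 14 / 27 / 43 | 11 / 20 / 32 | 7 / 12 / 16 |
| 1.5 | 0.3 | 13 / 24 / 38 | 5 / 5 / 6 | 5 / 5 / 5 |
| 1.5 | 0.5 | 7 / 10 / 14 | 8 / 12 / 18 | 6 / 8 / 11 |
| 1.5 | 0.7 | 5 / 5 / 5 | 20 / 40 / 63 | 13 / 24 / 39 |

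No form of change is safe throughout. The partial correlation of marker and raw change given the starting score rejects in about 5% of runs in every cell.

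**Step 3: precision.** Residual variance with the starting score in the model, relative to the variance of raw change:

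k²(1 − ρ²) / (1 + k² − 2ρk)

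- k = 1: 0.65, 0.75, 0.85 for ρ = 0.3, 0.5, 0.7.
- k = 1.5: 0.87, 0.96, 1.00.

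For a marker that splits patients 67 and 67, an effect with 80% power on raw change (d = 0.488) has power 94%, 90% and 86% at k = 1 after dividing d by the square root of the ratio. At a ratio of 1.00 it stays at 80%. This contrast uses the marker as the grouping variable. It is not the responder comparison on which the sample size rests.

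**Step 4: the opposite null.** The 5% for the partial correlation follows from the assumed null. Suppose instead that start and end scores both measure a stable true severity with error, the marker tracks that true severity, and everyone improves in parallel. With k = 1 and the same ρ and r, raw change then rejects in about 5% of runs and the partial correlation in about 17 to 97%.

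**The case against.** The strongest reply is that much of this is read into silence. A reader might infer that the plan uses raw differences and carries no starting score anywhere. The article supports neither. It speaks only of changes, next to a responder contrast. Its covariate list is open. Regressions stand in the same first step as the correlations, and mixed models follow; both can hold a baseline term. A fuller protocol or analysis plan may complete the list. Nor does the article say that a marker must pass the correlation step to reach the models.

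That disposes of any claim that baseline is ignored throughout. It does not rescue plain Pearson correlations and correlation matrices, which cannot hold a covariate and are stated choices. Repeated-measures ANOVA does not cure it either: with two time points, its marker-by-time test is the same as an unadjusted analysis of change.

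Second, the hypotheses mostly concern changes in the markers, in an exploratory study whose stated focus is change within subjects. This is fair and limits the point to pre-treatment measures used as predictors, which the plan does include.

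Third, a reader might conclude that change scores should be abandoned. Step 4 shows why not: which analysis misleads depends on how marker, true severity and recovery are related, and the article cannot settle that.

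**Conclusion.** The point holds in limited form. The plan makes symptom change the main outcome, relates pre-treatment markers to it partly by unadjusted correlation and ANOVA, and names covariates without the pre-ECT score. A marker of starting severity can therefore pass as a predictor of response.

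Its size cannot be fixed from the article. For raw differences the false-predictor rate is about 14 to 79% with equal SDs and about 5 to 38% at an SD ratio of 1.5. For percent change or a 50% responder split it is about 5 to 63%. These figures hold only under the assumed ρ, r, SD ratios and means, and under the null that the marker carries nothing beyond the measured starting score. Precision may be lost: adjustment cuts residual variance by 15 to 35% with equal SDs, but by almost nothing at an SD ratio of 1.5 and ρ = 0.7. A definite loss of power, or a fixed false-positive rate such as 42%, would go beyond what the article supports.

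**What to change.** In the Prospective statistical analysis section, for analyses of pre-treatment markers as predictors of outcome:

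- Add the pre-ECT score of the same scale as a covariate in the linear and logistic regressions and in the mixed models. In the mixed models, that score should then be a covariate and not also one of the repeated outcomes.
- In the screening step, use partial correlations given that score.
- State the form of the change, and confirm that the week-1 rating precedes the first ECT session.

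Keep the analyses of within-subject change for the change question, labelled as unadjusted for starting severity. In a linear regression the outcome need not be redefined: once the starting score is in the model, the marker coefficient is the same for the later score and for the raw difference.

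The cost is wording and one degree of freedom per model; the scores are already scheduled. The downside is measurement error in the starting score. An adjusted association shows prognostic value beyond measured baseline severity. It does not prove that the marker affects response.

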In study participants, serial venous blood draws (prior fasting: ≥ 6 h) are performed before and after the first and seventh as well as after the twelfth ECT session. A detailed schematic of the study design is given in Fig. 1. Pre-ECT blood draws with a total volume of 36 ml include collection of ethylenediamine tetra acetic acid (EDTA) (Sarstedt, S-Monovette® K3 EDTA) and serum (Sarstedt, S-Monovette® Serum Gel) tubes as well as PaxGene Blood RNA Tubes (Qiagen) for the extraction and analysis of DNA and epigenetic measures (e.g., methylation patterns), RNA including messenger and micro-RNA (mRNA and miRNA, respectively), neuron-derived exosomes, purines, hormones, proteins, electrolytes, metabolic parameters, inflammatory markers, and peripheral blood mononuclear cells (PBMCs). Post-ECT blood draws include only EDTA and serum tubes (Sarstedt) for total of 10 ml. In a subset of *n* = 10 participants, which are recruited at the very beginning of the study’s field phase (DetECT pilot phase), the ECT blood collection after the first ECT consists of three time points (1 h, 3 h, and 6 h post). The rationale for this schedule is to characterize the temporal post-ECT dynamics. This would also allow to discriminate between an immediate ECT-induced release of brain-derived molecules and cells through the blood–brain barrier (fast pathway) or a delayed release via cerebrospinal fluid drainage (slow pathway). To achieve this, the pilot phase materials and data are analyzed with regards to the different multiomics read-outs to determine the optimal post-ECT time point for the study main phase. To reduce batch effects, samples are stored in the MPIP’s biobanking unit in freezers for later analyses with larger sample sizes.

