## Longitudinal psychometric measures

To simultaneously measure depressive, neurocognitive, and somatic symptoms longitudinally in DetECT participants, we have selected four self-rating and three clinician-rating instruments. Since DetECT patients suffer from severe TRD and are thus heavily affected, psychometry was tailored to minimize participant efforts, while maximizing read-outs and item validation options post hoc. Only German questionnaire versions were used (see [126, 131, 137–140]).

Self-rating questionnaires: The PHQ-9 and PHQ-15 are both subscales of the patient health questionnaire (PHQ), which have proven effective for monitoring depression and somatic symptom burden [141]. The PHQ-9 is a self-administered depression screening, which contains a dimensional answer category (0 = not at all; 3 = nearly every day) for the nine depression criteria derived of the DSM-IV [123, 142]. The BDI-II is, similar to the PHQ-9, a multiple-choice self-report questionnaire with high validity and reliability [127–129, 143]. It is composed of 21 items, which have values of 0 to 3, to assess the presence as well as severity of depression [127]. The PHQ-15, on the other hand, is a self-rating questionnaire to assess somatic symptom load via 15 questions (0 = not bothered at all; 2 = bothered a lot). Summary scores are used as indicators of somatic symptom burden [125]. The FLei is a comparatively novel measure of neurocognitive function. By use of 35 questions with answers ranging from 0 = never to 4 = very frequently, the following domains are assessed: (I) attention, (II) memory, (III) executive functions, (IV) control scale [126]. Based on the FLei domain and sum scores, a longitudinal neurocognitive profile can be computed.

Clinician-rating questionnaires: Both, the MADRS and HAM-D21 are obtained by trained study personnel in a clinical interview. The MADRS (10-question instrument) and the HAM-D21 (21 items) both assess depression presence and severity [130–134]. The GAF is a functionality and severity score for psychiatric disorders ranging from 0 (= maximum symptom severity and load, extreme sociofunctional impairment) to 100 (= no symptoms or impairment). The index accounts for overall psychiatric symptom severity and sociofunctional impairment [135, 136].

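### The longitudinal method named for the first analysis step, repeated-measures ANOVA, keeps only patients complete on each model's time points; the mixed model already planned could do that job

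*Protocol article*

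**What the plan says.** The section Prospective statistical analysis takes clinical response, measured by psychometric change, as the main dependent variable and concentrates on change within subjects over time. It describes two steps.

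- **First step.** "we aim to use variance and correlation analyses (e.g., repeated-measures ANOVA", with Pearson correlation and correlation matrices as further examples, followed by "regression models (e.g., linear or logistic regression), and principal component analysis to first identify both significant main and interaction effects". On scope: "These analyses will be performed for all measures pre-, during, and post-treatment". Area under the curve and index scores are also to be used.
- **Second step.** "Following these steps, we plan to employ linear mixed models (LMM) to examine if a single or parameter cluster is linked to remission", as well as to response, failure and side effects.

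The repeated series come from Study design and population. Self-ratings: "participants are asked to answer the following self-rating questionnaires concerning their depressive and somatic symptoms on a weekly basis". Blood draws "are performed before and after the first and seventh as well as after the twelfth ECT session". Clinician ratings are taken in weeks 1, 4 and 7. Of the patients, Longitudinal psychometric measures says: "Since DetECT patients suffer from severe TRD and are thus heavily affected".

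Power calculation arrives at 134 patients. The recruitment target is the same number (10 pilot plus 124 main-phase patients), with no stated allowance for loss.

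**The concern.** Of the methods named for the first step, repeated-measures ANOVA is the only one built for a repeated within-subject factor, so it is the natural carrier of the group-by-time tests. Its classical form needs a full row per patient. One missing level of the time factor removes all of that patient's other values from that model.

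Two features of the study make gaps plausible and possibly informative. The patients are severely ill, so a skipped self-rating may depend on current depression. Treatment follows clinical care, and the Introduction says remission under ECT often comes at about three weeks, so later ratings or draws may also be missing because a patient has done well. In either case missingness would be tied to the outcome. The two mechanisms can pull in different directions, so the direction of any bias is not known in advance.

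At stake are the precision and representativeness of the first-step longitudinal results. The study's objective concerns TRD patients receiving ECT, not only those with complete series.

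**Working it through.** **Step 1: the plan's own figure.** Inputs from Power calculation: d = 0.5, α = 0.05, power 0.80, responders versus non-responders. The test, its sidedness and the group ratio are not stated; two-sided and 1:1 are assumed here.

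- Two-sample t-test (noncentral t): 63.77 per group, rounded up to 64, total 128.
- Wilcoxon–Mann–Whitney with asymptotic relative efficiency 3/π: 63.77 × π/3 = 66.78, rounded up to 67, total 134.

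So 134 is reproduced exactly as a two-sided rank-test calculation. With 67 per group, the t-test has power 0.819.

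**Step 2: occasions per patient (k).**

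- Weekly self-ratings over about 7 weeks: k ≈ 7.
- Blood draws: before and after ECT 1, before and after ECT 7, after ECT 12: k = 5. This is an upper figure for the main phase, because post-ECT draws contain only EDTA and serum tubes, so some markers have fewer occasions.
- Clinician ratings: k = 3.

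**Step 3: complete series.** The article gives no missing rate. Assume a share q of occasions is missing, independently. Then complete patients = 134 × (1 − q)^k. For example, 134 × 0.95^7 = 134 × 0.698 ≈ 94. Power in brackets is for a two-sample t-test at d = 0.5, two-sided α = 0.05, equal groups.

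| Series | q = 2% | q = 5% | q = 10% |
|---|---|---|---|
| 7 weekly ratings | 116 (0.761) | 94 (0.669) | 64 (0.504) |
| 5 draws | 121 (0.779) | 104 (0.714) | 79 (0.593) |
| 3 clinician ratings | 126 (0.795) | 115 (0.757) | 98 (0.688) |

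At q = 1% the counts are 125, 127 and 130, so the loss is slight. For a simple before/after pair (k = 2), 134 × 0.98² ≈ 129 and 134 × 0.95² ≈ 121 remain.

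The bracketed values only put the counts on the scale of the article's own sample-size calculation. They are not the power of the repeated-measures ANOVA itself.

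**Step 4: if gaps cluster within patients.** Independence is the pessimistic case. Take a beta-binomial model with 5% missing, k = 7 and within-patient correlation ρ. With a + b = 1/ρ − 1 and a = 0.95(a + b), the complete share is the product over i = 0,…,6 of (a + i)/(a + b + i).

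- ρ = 0.2: a = 3.8, a + b = 4, share 0.800, 107 patients (power 0.73).
- ρ = 0.4: a = 1.425, a + b = 1.5, share 0.856, 115 patients (power 0.76).

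Both exceed the 94 under independence.

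**Step 5: what each first-step method needs.** Repeated-measures ANOVA needs every time point in its model. A correlation or regression at one time point needs only the values it uses. Deletion acts model by model: a skipped questionnaire does not remove a patient from an ANOVA of blood draws, nor the reverse.

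**The case against.** The strongest reply is that repeated-measures ANOVA is only an example, listed beside correlations, regression and principal components in an exploratory study, and that mixed models are planned anyway. Much of this stands, and it rules out three stronger readings.

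- **That the whole first step runs on completers.** A reader might infer this, but cross-sectional correlations and regressions do not need complete series.
- **That markers missed in the first step never reach the mixed models.** The wording gives an order, not a filter. The mixed models are also to use single, combined and over-time parameters, and the Abstract presents conventional statistics and mixed models side by side.
- **That much of the sample of 134 will be lost.** No figure in the article supports this. The loss is large only at roughly 5% or more missing per occasion on the longer series.

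It is also fair that imputation and missing-data rules commonly sit in a full protocol or SAP, so their absence from an article is no fault, and that an imputation rule there could avoid the deletion. That does not dispose of the point, which concerns a method the article does name. Even without a filter, the first-step longitudinal results would by default rest on complete series when a method without that restriction is already in the plan.

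**Conclusion.** The point holds in limited form. Where classical repeated-measures ANOVA is used in the first step, each model is restricted to patients complete on its own time points. Its group-by-time results can then be less precise, and they may be biased toward completers if gaps relate to severity or response.

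The size cannot be fixed from the article. Under independent missingness of 2% to 10% per occasion, complete patients would number 116 to 64 for weekly ratings, 121 to 79 for five draws and 126 to 98 for clinician ratings, and more than that if gaps cluster. No size or direction of bias can be given without assuming a missingness mechanism. Because the computed and recruited numbers are both 134, no stated allowance for loss sits above the target.

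This is a cheap improvement to a named method. It does not show that the planned analyses fail.

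**What to change.** In Prospective statistical analysis, for longitudinal tests in the first step, replace repeated-measures ANOVA with the likelihood-based linear mixed model already planned for the second. Include time, response group or marker, and their interaction, and fit it to all available outcome values, keeping patients with gaps. Retain complete-case repeated-measures ANOVA, if wanted, only as a sensitivity analysis. Cross-sectional correlations and regressions can stay as they are.

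The cost is one wording change and slightly more model fitting, with no extra patients or data. Two limits should be acknowledged. The model relies on missing-at-random, which is weaker than what complete-case ANOVA generally needs but is still an assumption. It also accommodates missing outcomes, not missing predictors: where a marker is the independent variable, rows without that draw still drop out.

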## Study hypotheses and objectives

The primary hypothesis of the DetECT study is that there exists a joint biological function and clinically meaningful connection between changes in gene expression and regulation, immunometabolic conditions, purinergic signaling, and CNS-derived exosome release in TRD patients receiving ECT. The secondary hypothesis is that these changes can be utilized to predict and monitor ECT outcome in TRD patients.

The main study objective is therefore to identify biological, psychological, socioeconomic, and clinical parameters (biomarkers) that provide detailed information about the general or individual factors of ECT success and the biobehavioral disease subgroups these changes are linked to. The DetECT data may also serve as a cornerstone for the development of a biologically founded, multimodal prognosis model for ECT use in TRD. As a subordinate objective, we hope to generate novel insight into the molecular effects of ECT in TRD using the generated omics data. Taken together, we believe that the DetECT results can aid precision medicine approaches for ECT application and to boost its social as well as clinical acceptance.

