## Power calculation

In complex psychiatric illnesses, such as MDD, which arise from the reciprocal interaction of endogenous and exogenous influences (interaction: genes x environment) [159], the effect of single parameters is small. Only the interaction of many and qualitatively heterogeneous components leads to the disease. The best-known explanatory model is the diathesis-stress model, in which the interaction of individual vulnerability (biological and psychosocial) and external influences is acknowledged. Therefore, and due to the exploratory and multiomics approach of the DetECT study focusing on unstudied parameters, sample size calculation cannot simply be performed based on preexisting study results. Accordingly, we have based our power calculation on the clinical ECT efficacy [55, 56], as it is a composite indicator of the interplay of multiple ECT-induced biological mechanisms and their effect sizes, respectively. Using G*Power 3 Software comparing responders with non-responders assuming a moderate effect size of *d* = 0.5, a significance level *α* = 0.05, and a power of 1–*β* = 0.8, we computed a sample size of *n* = 134 [160].

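### Effect sizes reported after a significance screen in the same 134 patients are biased upward, and a multiplicity correction at the screen enlarges that bias

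*Protocol article*

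**What the plan says.** The analysis section of the protocol article "mainly focuses on comparing ECT responders with non-responders (internal control group) within the sample". Its main dependent variables are changes in psychometry that indicate clinical response.

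- **Step 1.** ANOVA, correlation, regression and principal component analyses are used "to first identify both significant main and interaction effects between biobehavioral parameters and treatment response". They are run on measures from before, during and after treatment. Independent variables are described thus: "Aside from using single parameters and the area under the curve as independent variables", together with indices and scores.
- **Step 2.** "Following these steps, we plan to employ linear mixed models (LMM) to examine if a single or parameter cluster is linked to" remission, response, failure and side effects. No second sample is named.
- **Safeguards.** A multiple-comparisons correction is promised, without method, family or stage. Reporting effect sizes beside p values is then offered as the way to make sure that an association is biologically relevant and not merely significant.
- **Aims.** Under Study hypotheses and objectives: "The secondary hypothesis is that these changes can be utilized to predict and monitor ECT outcome in TRD patients". The Study timeline makes clinical implementation of the identified biomarkers a focus of phase four.

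**The concern.** If a marker is carried forward because its difference between responders and non-responders passed a significance threshold, the size of that difference in the same patients is no longer a fair estimate. Only markers whose estimate exceeded the threshold are seen. The effect size is therefore least trustworthy in the role the plan gives it, as evidence that a selected marker matters. The Power calculation section itself expects single parameters to have small effects, and that is where the bias is largest.

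Two further matters bear on the predictive aim. If the correction does not cover the screen, a cluster built from chance findings can look discriminating. And the plan does not say which time points may support a claim of prediction. The last blood sample falls within a week after the twelfth session and the last clinician rating in week 7, so that sample, and any area under the curve over the whole course, is concurrent with or later than the outcome.

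At stake are inflated marker effects taken into replication studies and clinical use, and markers that accompany improvement being described as predicting it.

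**Working it through.** **1. The plan's own figure.** The inputs are "assuming a moderate effect size of *d* = 0.5, a significance level *α* = 0.05" and "a power of 1–*β* = 0.8"; the plan states "we computed a sample size of *n* = 134". The test and its sidedness are not given.

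- Two-sided t test, equal groups: 64 per group, total 128 (power 0.801).
- Two-sided Wilcoxon-Mann-Whitney test, normal data, efficiency 3/π = 0.955: 64 / 0.955 ≈ 67 per group, total 134 (power 0.801).

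The figure is reproduced by the second variant. It covers one pre-chosen comparison at α = 0.05. It makes no allowance for choosing markers from a panel.

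**2. Effect size after selection.** Assumptions: 80/54 split (80/134 ≈ 60% response, inside the 56–85% quoted in the Introduction), two-sided t test, true d = 0.3, and 50 to 1,000 candidate markers. The article gives no marker count.

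- The estimate is d̂ = t / c, with c = √(80 × 54 / 134) = √32.24 = 5.678.
- t follows a noncentral t distribution with 132 degrees of freedom and noncentrality 0.3 × 5.678 = 1.70.
- A marker is seen only if |d̂| exceeds t_crit / c. The mean reported d is the mean of d̂ given that it passes.

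| Screen | t_crit | Smallest d that can pass | Chance that a true d = 0.3 passes | Mean reported d |
|---|---|---|---|---|
| p < 0.05 | 1.978 | 0.35 | 39% | 0.48 |
| Bonferroni, 50 | 3.366 | 0.59 | 5% | 0.67 |
| Bonferroni, 200 | 3.765 | 0.66 | 2% | 0.73 |
| Bonferroni, 1,000 | 4.194 | 0.74 | 0.8% | 0.80 |

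At every threshold the smallest passing estimate is above the true value. A true d of 0.2 is reported as 0.45 at p < 0.05. The planned d of 0.5 is reported as 0.77 under Bonferroni over 200 markers.

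**3. Pure noise, screen uncorrected.** Simulation with N = 134, 70% response and independent normal markers with no true effect. At most 10 markers with p < 0.05 are kept and combined by a linear discriminant (100 runs per setting). About 0.05 × the number of candidates pass by chance, for example 0.05 × 200 = 10.

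| Candidates | Apparent ROC AUC, same patients | AUC, new patients |
|---|---|---|
| 20 | 0.64 | 0.50 |
| 50 | 0.68 | 0.50 |
| 100 | 0.76 | 0.50 |
| 200 | 0.84 | 0.50 |
| 1,000 | 0.90 | 0.49 |

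Under the same rule the apparent AUC runs from 0.64 to 0.88 at 56% response and from 0.69 to 0.95 at 85%.

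**4. Pure noise, screen corrected.** With Bonferroni or Benjamini-Hochberg over 50, 200 or 1,000 markers, any noise marker passes in only about 4–5% of studies. The apparent AUC is then about 0.69–0.73.

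**5. Selection repeated inside validation.** With the screen repeated in each fold of a 5-fold cross-validation, the AUC of the uncorrected noise clusters returns to about 0.50 (0.48–0.54 across all settings tried).

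**The case against.** The strongest reply is that the article does promise a multiple-comparisons correction. If it is applied at the screen, the noise scenario largely disappears (step 4). That stands, so one should not conclude that the planned analysis will yield a convincing cluster when there is no signal. The article leaves the stage open. The correction also does nothing for the effect sizes; step 2 shows that it makes them worse.

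Other points in the plan's favour:

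- A reader might infer that internal validation has been ruled out. The document does not support this. It is a condensed article, and cross-validation or bootstrap may be set out in a fuller plan. The point rests on the stated sequence and the stated role of effect sizes, not on that silence.
- The plan specifies no ROC AUC. Its area under the curve is a summary of a marker over time, used as an independent variable. The AUC values above illustrate the problem under assumed marker counts and are not figures for this trial.
- The article does not say that only significant parameters enter the mixed models, and principal components or functional indices need not be selected on response. The order of the steps still makes selection the natural reading, and the bias applies to any effect size that is reported because it was significant.
- Samples during and after treatment suit monitoring and the study of mechanism, both of which are stated aims. Using them is not an error. What is absent is a line between those uses and prediction.
- The design is exploratory and the outlook is worded cautiously. That tempers the concern, but prediction is nevertheless the secondary hypothesis and implementation a stated focus.

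**Conclusion.** The point holds in a limited form. Significance against response comes first, modelling in the same 134 patients follows, and effect size is asked to vouch for relevance. An uncorrected effect size from the selecting data cannot do that. With an 80/54 split, a true d of 0.3 would be reported as about 0.48 after an uncorrected screen and as 0.67 to 0.80 after Bonferroni over 50 to 1,000 markers. The split and the marker counts are assumptions, but the direction of the bias does not depend on them.

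It would go too far to say that noise will look predictive in this study. An apparent AUC of about 0.65 to 0.9 from noise requires an uncorrected screen, and its height depends on the assumed number of candidates. The pooling of time points is a separate and lesser matter: it leaves the meaning of prediction open but does not by itself create false discrimination. This should be settled before the main-phase data are analysed. It does not call the data collection into question.

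**What to change.** - State that the multiplicity correction applies at the screening step, and name its method and the family of tests it covers.
- Repeat the whole selection inside cross-validation or a bootstrap, and report optimism-corrected performance and effect sizes. Do not present the uncorrected effect size of a selected marker as evidence of relevance.
- Base any claim of prediction only on samples taken before the outcome. Two landmarks fit the schedule: samples up to the first ECT, and samples up to the draw before the seventh ECT with adjustment for symptom change so far.
- Report areas under the curve over the full course and values after the twelfth session as monitoring markers or correlates of response.

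The cost is more computing, some added wording in the analysis plan, and less favourable reported performance. No new patients, visits or samples are needed.
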